### 6.2.1 Primary outcome

Percentage of PLWHA intending to receive the HPV vaccine.

### 6.2.2 Secondary outcome

Vaccination initiation rate (at least one dose of vaccine) among PLWHA and complete vaccination rate (three doses of vaccine).

### 6.2.3 Sample size

The goal will be to enroll 836 to 650 participants (assuming a 30% to 10% dropout rate) or 586 evaluable participants. By obtaining a sample of 293 evaluable patients per group and adopting a type I error probability (alpha) of 5%, we will have 80% power to detect a difference of 10% (20% vs. 30%) or greater between the intervention group and the control group.

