A study examined the theoretical determinants of HPV vaccination intentions by assessing the PMT and theory of planned behavior (TPB) constructs in three groups: college women, parents of daughters, and parents of sons. The results indicate that the PMT and TBP constructs predict intentions for the different groups. Focusing on vaccine response efficacy, rather than perceived HPV severity, was most effective in increasing vaccination intentions among all groups. Focusing on HPV vulnerability was effective only among college women and parents of sons, and self-efficacy predicted intentions among college women and parents of daughters (GAINFORTH, CAO, and LATIMER-CHEUNG, 2012) .

A pilot study to test an HPV vaccination intervention among 150 young gay and bisexual men aged 18 to 25 showed that HPV vaccination initiation was higher among those who received HPV information based on the PMT constructs (45% vs. 26%). This same group also showed a higher tendency to complete the full vaccination schedule (11% vs. 3%) (REITER *et al.* , 2018) .

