### 6.1.3 Effectiveness

The effectiveness of the intervention (E) will be obtained by the percentage of participants who declared their intention to get vaccinated. Measured by the ratio between the sum of the number of participants who declare that they will or intend to get vaccinated ( nV ) and the number of participants in the groups randomized to their respective *websites* ( nP ).

$$= \frac{\text{---}}{\text{---}} \times 100$$

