## 6.2 DATA ANALYSIS METHODOLOGY

A descriptive analysis of the frequency distribution of the main outcome variables and other variables will be performed. Continuous variables will be expressed as mean  $\pm$  standard deviation with a 95% confidence interval (CI), and categorical variables will be expressed as frequencies and percentages. To assess the effects of the intervention on the intention to get vaccinated (effectiveness), the groups will initially be assessed for sample homogeneity in relation to demographic and health-related characteristics. Differences between the groups studied will be calculated using *Student's t-test*. for quantitative variables and, for categorical variables, the comparison between groups will be performed using the Chi-square test. The logistic regression model will be used to compare the study groups in all outcomes, adjusting for potential confounding variables . Statistical analyses will be performed using the *software* Stata 12. P-values <0.05 will be considered statistically significant.

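### The 80% power is computed on evaluable participants, but the primary percentage is defined over all randomised; on that definition the planned enrolments give 76% to 79%

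*Protocol*

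**What the plan says.** Section 6.2.3 sizes the trial on participants who remain after dropout: "By obtaining a sample of 293 evaluable patients per group", the protocol says, "we will have 80% power to detect a difference of 10% (20% vs. 30%) or greater". The enrolment goal is a range linked to assumed loss: "The goal will be to enroll 836 to 650 participants (assuming a 30% to 10% dropout rate) or 586 evaluable participants".

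Section 6.1.3 defines effectiveness, the primary percentage, as a ratio. The numerator is the number who declare that they will or intend to be vaccinated. The denominator is "the number of participants in the groups randomized to their respective" websites.

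Section 5.6 puts the intention question at the moment a participant starts the Get vaccinated section. On the intervention site this is the last of four sections (section 5.4). A person who leaves earlier has been randomised but gives no answer.

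The protocol does not define evaluable or dropout, and nothing in it reconciles the two bases.

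**The concern.** The sample size calculation removes dropouts; the definition of the primary percentage keeps them. Under section 6.1.3 a randomised participant without an answer is in the denominator but cannot be in the numerator, and so counts as not intending. Both group percentages shrink by the proportion lost, and so does their difference. Dividing 586 by one minus the dropout rate makes up the number of answers, but the added participants are diluted in the same proportion.

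The power figure in section 6.2.3 therefore belongs to a different analysis from the one section 6.1.3 defines. There is also a question of interpretation. If loss differs between two sites that differ in content and design, the two denominators can give different answers, and the protocol should be clear beforehand which one carries the primary conclusion.

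**Working it through.** **Inputs.** From section 6.2.3: rates of 20% and 30%, alpha 5%, power 80%, 293 evaluable per group, enrolment of 836 (30% loss) or 650 (10% loss). From section 5.3: 1:1 allocation. From section 6.2: chi-square test, with "P-values <0.05 will be considered statistically significant". Sidedness is not stated. I take it as two-sided because that reproduces the protocol's figure; one-sided would give 231 per group.

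**Formula.** Pooled two-proportion test without continuity correction, n per group, p̄ = (p1 + p2)/2:

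power = Φ{ [ (p2 − p1)√n − 1.96·√(2p̄(1 − p̄)) ] / √(p1(1 − p1) + p2(1 − p2)) }

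**Step 1: reproduce the protocol.**
- For 20% versus 30%, 80% power needs n = 293.15 per group.
- At n = 293: (1.7117 − 1.96 × 0.6124)/0.6083 = 0.841, power 79.98%.
- Enrolment: 586/0.7 = 837 and 586/0.9 = 651, against 836 and 650 stated. The difference of one is immaterial.

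The calculation is correct for evaluable participants.

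**Step 2: apply the section 6.1.3 denominator.** Assume that 20% and 30% hold among evaluable participants and that a proportion d is lost equally in both arms. The rates over all randomised are then 20%(1 − d) and 30%(1 − d), and n is everyone randomised to the group.

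- 836 randomised, d = 30%: n = 418, 14% versus 21%. (1.4312 − 1.96 × 0.5374)/0.5351 = 0.706, power 76.0%.
- 650 randomised, d = 10%: n = 325, 18% versus 27%. (1.6225 − 1.96 × 0.5906)/0.5871 = 0.792, power 78.6%.

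**Step 3: the pairings not planned.**

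| Randomised | Loss | Rates over all randomised | Power |
|---|---|---|---|
| 650 | 30% | 14% vs 21% | 65.2% |
| 836 | 10% | 18% vs 27% | 87.8% |

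On evaluable participants alone, 650 with 30% loss leaves 650 × 0.7 = 455 and 69.4% power.

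**Step 4: what 80% would need on the section 6.1.3 definition.** 337 per group (674 in all) at 10% loss, and 462 per group (924 in all) at 30% loss. The second figure exceeds the stated maximum of 836.

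**Step 5: the alternative reading of the rates.** If 20% and 30% were meant over all randomised, power would be 83.9% with 650 and 91.7% with 836.

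**The case against.** Four points can be made for the protocol.

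*The rates may already be over all randomised.* Power would then exceed 80% throughout (step 5). But section 6.2.3 attaches the rates to evaluable participants, and on this reading the inflation for dropout would have no purpose. The point stands as an assumption to be stated.

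*Dropout may not mean a missing primary answer.* The primary question is asked during the browsing session, whereas vaccination initiation and completion (section 6.2.2) come later. If part of the 10% to 30% is loss to those later outcomes, the dilution is smaller. This is fair, and the protocol's silence on the term leaves it open.

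*The enrolment range is conditional.* Section 6.2.3 pairs 836 with 30% loss and 650 with 10%, both leading to 586 evaluable. A reader might infer that the design delivers only 65%, or 65% to 79%. The text does not support that: those figures describe an enrolment of 650 only, stopping there with 30% loss would miss the protocol's own 586, and 836 with 10% loss gives 88%. What remains is that the stopping rule is not put into words.

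*The base rate is declared.* A reader might also infer that 20% is too low for the control group, because the pilot cited in section 3.4 had 26% of its comparison group starting vaccination. That does not follow. The pilot enrolled gay and bisexual men aged 18 to 25 and measured initiation, not three-month intention in people with HIV aged 18 to 45. Its contrast, 26% versus 45%, was also much larger than 10 points and would have 99.8% power at 293 per group. Section 6.2.3 states 20% versus 30% openly, and that choice is not an error.

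Nor does the protocol declare two primary analysis sets. Section 6.1.3 gives one denominator, and section 6.2.3 is a sizing statement that does not match it. Further handling of missing answers can be left to a SAP; the mismatch lies within the protocol itself.

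**Conclusion.** The point holds as a mismatch between two current sections. The 80% is correctly computed for 293 evaluable participants per group, but the primary percentage as defined has 76% power at 836 randomised with 30% loss and 79% at 650 with 10% loss. The shortfall is small, about 1 to 4 percentage points. The 65% figure is a warning about what would happen if the lower enrolment met the higher loss; it does not describe the plan.

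The figures assume a two-sided 5% test, rates of 20% and 30% among evaluable participants, equal loss in both arms, all dropout being loss of the primary answer, and no answer counting as not intending. The last follows from the ratio in section 6.1.3 but is not said in words.

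**What to change.** 1. In sections 6.1.3 and 6.2.3, use one denominator: all participants randomised to each website, with no answer counted as not intending, as section 6.1.3 already implies. Define evaluable as having answered the intention question, and name the analysis of evaluable participants as a sensitivity analysis.
2. In section 6.2.3, state that 20% and 30% are rates among evaluable participants, and give the power for the primary definition as 76% (836 randomised, 30% loss) and 79% (650 randomised, 10% loss).
3. State that recruitment continues until 586 evaluable participants are reached, up to a maximum of 836 randomised. If a single stop at 836 is preferred, give the power as 76% (30% loss) to 88% (10% loss).

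The cost is mainly wording, and a stated power slightly below 80%. A fixed stop at 836 would mean up to 836 − 650 = 186 more participants than the low end of the present goal. Nothing here requires enrolment above the current maximum.

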## 7. SCHEDULE

| DESCRIPTION |                                                                       |
|-------------|-----------------------------------------------------------------------|
| 2021 | Submission to CEP ( February )                                        |
|             | Finalize prototype ( April )                                          |
|             | Focus Group Discussion ( May )                                        |
|             | Prototype review and adjustments after focus group discussion ( May ) |
| 2022 | Data collection (January to June)                                     |
|             | Data analysis (October to November)                                   |
|             | Preparation of the thesis and article ( November to December)         |

## 8. BUDGET

The project will have a relatively low cost, therefore, it will be executed with the advisor's own resources and the CNPq bench fee. Equipment (computers, tablets, etc.) and LEMB software will be used to conduct data analysis.

| Item                                       | Amount | Total               |
|--------------------------------------------|--------|---------------------|
| Ream of paper                              | 1      | 57.90               |
| Web Designer Consulting                    | 40hs   | 1,800.00            |
| Social Communication Specialist Consulting | 40hs   | 1,800.00            |
| TOTAL                               |        | R\$ 3,657.90 |

## 9. ETHICAL CONSIDERATIONS

All Guidelines and Regulatory Standards for Research Involving Human Beings - Resolution No. 466/2012 of the National Health Council will be followed. The principles of bioethics (autonomy, non-maleficence, beneficence and justice) will be respected. (CNS, 2012) . For the purposes of this study, research participants will be informed about the objectives and content of the research in accessible language on an *online form* . Therefore, it will not be possible to apply a signed version of the Free and Informed Consent Form (FICF). They will also be informed that participation in the study is completely voluntary and that consent to participate in the study may be withdrawn at any time. No participant may enter the study before consent has been obtained

The study protocol and other relevant documents will be submitted to the Research Ethics Committee for collegiate evaluation and approval. The database will be created without information about the identity of the study participants, therefore all analyses will be performed anonymously and with the privacy of the subjects included in the research guaranteed. The information collected will be used only for the purpose of the study and the results found will be published in scientific journals in the area.

### 9.1 ASSESSMENT OF RISKS AND BENEFITS:

#### 9.1.1 Risks

Risk of embarrassment with some questions. However, this is mitigated by the fact that the participant will be able to do so in privacy since it is an *online questionnaire* .

#### 9.1.2 Benefits

Benefit for the individual who, by participating in the study, may choose to receive the vaccine. Secondly, the individual, being at the vaccination center, also tends to update the vaccination card, receiving any doses that may still be pending.

Identification of a more effective approach to promoting the HPV vaccine among PLWHA.

In addition, the study will generate a product that will be freely available for use and adaptation: the iHPV intervention . In addition, the work provides a guide for the production of relevant and efficient information since it will identify the TMP constructs and content related to HPV and the HPV vaccine that most captured the attention of the key population.

